## Abstract

**Methods:**

The POI trial is a cluster‐randomized controlled study conducted in primary schools in Gran Canaria, enrolling children aged 6–10 years. The intervention integrates nutrition education, physical activity promotion, and family engagement, supported by both paper‐based and digital educational materials. Teachers played a central role in intervention delivery within the classroom setting. Schools served as the unit of randomization and implementation. Baseline assessments included standardized anthropometric measurements, objectively measured physical activity, and selected metabolic parameters (fasting glucose and lipid profile). Dietary intake outcomes will be reported separately; this manuscript focuses on the nutrition education framework and baseline nutrition‐related metabolic indicators.

**Results:**

A total of 557 children from 13 schools were included (298 intervention participants from 5 schools and 259 controls from 8 schools). Significant differences in overweight and obesity prevalence were observed by school type, with the highest prevalence in public schools (48.6%), followed by partially subsidized (33.2%) and private schools (28.3%) (*p* = 0.001). Among participants with available blood samples (*n* = 237), elevated fasting glucose was detected in 21 children and hypercholesterolemia in 24 children.

**Conclusions:**

These baseline findings highlight substantial socioeconomic disparities in childhood overweight and obesity and demonstrate the presence of early metabolic risk in school‐aged children. The POI trial provides a scalable, school‐based model integrating nutrition education and physical activity for obesity prevention, with the potential to inform public health strategies in high‐prevalence settings.

**Trial Registration:** ClinicalTrials.gov identifier: NCT06607159

## 1. Introduction

Overweight and obesity are forms of malnutrition characterized by excess calorie intake, which significantly impact population health with cumulative effects over the life course. Obese youth exhibit elevated cardiovascular risk factors and are more likely to remain obese into adulthood [1]. Furthermore, they face increased risks of respiratory distress, fractures, hypertension, and diabetes mellitus. These physical health issues are often compounded by mental health challenges, social stigma, discrimination, and difficulties in relationships, all of which can substantially diminish their overall quality of life [2].

Childhood obesity has reached epidemic proportions globally. According to the World Health Organization (WHO), around 1 in 3 children aged 6–9 years in Europe live with overweight or obesity [3]. To address this issue, the WHO Regional Office for Europe established the Childhood Obesity Surveillance Initiative (COSI) in 2007 [4]. COSI aims to monitor trends in overweight and obesity among primary school children aged 6–9 years across Europe using standardized anthropometric measurements. The initiative has grown to include 45 participating countries to date.

In Spain, the ALADINO (Alimentación, Actividad física, Desarrollo Infantil y Obesidad) study is conducted as part of the COSI framework. It has undergone four rounds so far (2011, 2013, 2015. and 2019), providing nationally representative data on the weight status of Spanish children aged 6–9 years [5]. By 2019, ALADINO reported a combined excess weight prevalence of 40.6%, a modest decrease from 2011 [5]. However, obesity rates remained high and did not decline significantly over this period. The enKid study [6], conducted between 1998 and 2000, showed that the Canary Islands had one of the highest rates of overweight and obesity among Spanish children aged 6–13 years (prevalence of overweight/obesity of 32.8%). The ALADINO study confirmed the severity of the situation, placing the Canary Islands among the regions with the highest childhood obesity prevalence not just in Spain, but globally.

Intervention measures are more effective the earlier they are taken and the pediatric age is an ideal window of opportunity [7]. Recent reviews conclude that a multidisciplinary approach that takes into account a variety of factors including nutrition, physical activity, sleep time, and psychological intervention is more effective than interventions focused on only one area [8]. There is also strong evidence for school‐based interventions, with additional home or community‐based intervention components [9], with the added benefit that the introduction of nutrition education in schools has been shown to be cost‐effective [10].

Of special interest is the role of the socioeconomic status (SES) on obesity. Several studies in developed countries, including Spain, have shown the impact it has on its prevalence, highlighting the role parental income and education have on overweight and obesity rates [11, 12].

Given the alarming rates of obesity and overweight in our child population, we have developed an intervention strategy, based on a multidisciplinary, school‐centered approach, which addresses nutritional education, physical activity, behavioral intervention techniques, and tools that facilitate the learning of healthy lifestyle habits in children between 6 and 10 years of age. This article describes our design and implementation framework for a school‐based intervention on healthy lifestyle habits combining school, family, and student‐level components among children aged 6–10 years. It also describes the baseline characteristics and initial socioeconomic (SES) disparities found in overweight and obesity prevalence in our population.

## 2. Methodology

### 2.1. Study Design

This is a parallel, cluster‐randomized, controlled trial designed to evaluate a school‐based intervention for childhood obesity prevention in the Canary Islands. The study protocol was designed following SPIRIT guidelines. It was preregistered at AsPredicted.org, hosted by the University of Pennsylvania (registration No. 44205).

### 2.2. Participants and Randomization Process

Boys and girls aged 6–10 years (1^st^ to 4^th^ grades of primary school) from public, state‐subsidized, and private schools on the island of Gran Canaria, Canary Islands, Spain, were recruited. The selection of schools was based on convenience. After obtaining a list of schools from contacts with the local diabetic association and members of the team, the project was explained and schools were invited to participate. After obtaining the consent from several schools, the inclusion in both arms of the study was randomized with a 1:1 ratio (even though we performed cluster randomization, the aim was to have a 1:1 participant ratio, not a 1:1 classroom ratio), and the parents of the students in the aforementioned classes were invited to participate. Finally, those children whose parents consented to their participation were included. To randomize the participant schools, we employed a stratified cluster randomization approach. First, we categorized schools into three types: public, private, and subsidized. In Spain, type of school (public, subsidized, or private) is a strong indicator of socioeconomic background, as documented in previous national studies. This classification has therefore been used as a proxy for SES in the current analysis (each type of school represents a different SES, with a spectrum ranging from the lowest SES in the public schools, to the highest in the private ones [11]). Although randomization was stratified by school type (public, subsidized, and private) to account for socioeconomic differences, perfect balance between intervention and control groups was not achieved. This was due to variability in school sizes and the decision to prioritize a 1:1 ratio of participants rather than number of schools. This approach was chosen to preserve statistical power while maintaining the integrity of cluster randomization.

Within each category, we assigned a random number to each school and then ranked them from highest to lowest based on these numbers. Given that we knew the number of children in each class, we started allocating schools with the highest random numbers to either the intervention or control arm, continuing this process until the target number of children in each arm was reached. This approach ensured a 1:1 ratio of participants between arms while maintaining randomization integrity, even though it could result in an unequal number of schools per arm. To maintain cluster integrity and reduce contamination bias, all children from a given school were assigned to the same study arm—a methodological strength in school‐based interventions. Randomization was performed by the main author ([name]) using a stratified cluster randomization method in Microsoft Excel, assigning random numbers and stratifying by school type.

### 2.3. Intervention Protocol

The project for the prevention of childhood obesity in the Canary Islands aims to improve knowledge, attitudes, and behaviors related to healthy lifestyle habits in the pediatric age group through an educational and participatory approach (based on recommendations on diet [13, 14], physical activity [15, 16], leisure time devoted to screens [17], and hours of sleep [18]). One of our main goals was to develop cost‐free strategies and tools for schools. To achieve this, we decided to involve teachers as the primary drivers of change and schools as the implementation sites for the study protocol. To this end, the pediatric endocrinology and gastroenterology units of the Complejo Hospitalario Universitario Materno Infantil de Las Palmas de Gran Canaria have collaborated with the group specializing in “Learning Difficulties, Psycholinguistics, and Information and Communication Technologies (DEAP&NT)” of the University of La Laguna (https://viinv.ull.es/grupos/1119/), which includes psychologists, teachers, and pedagogues among its members.

As a result of this collaboration, a protocol for teaching healthy lifestyle habits has been developed, aimed at school‐age children (initially between 1^st^ and 4^th^ grades of primary school), to be implemented transversally in schools. This protocol takes into account three levels of action: school, family, and pupils.a.Materials in paper format: these materials are mainly used in the classroom, although they can also be used at home. They have been designed according to the grade level and the level of competence of the students. These workbooks are based on the curricular contents linked to healthy lifestyle habits that should be worked on according to the school year as established in DECREE 89/2014, of 1 August, which establishes the organization and curriculum of primary education in the Autonomous Community of the Canary Islands [19]. Likewise, from an inclusive perspective, suitable materials have been designed for students with specific educational support needs (SEN) that make it difficult for them to access the written code (Figure 1(a)). While all levels included mentions of sleep hygiene, specific guided activities were only included at levels 0–1, based on age‐appropriateness and curricular alignment. Higher levels introduced sleep indirectly through discussions on lifestyle balance. The books can be found in the following link: https://www.fundacionmapfrecanarias.org/formacion-prevencion/actividades-didacticas/programa-obesidad-infantil-fmc/.b.Digital materials: gamification has been proven to motivate and promote improvements in the nutrition of children [20]. For our intervention, 6 games have been designed in application format aimed at increasing daily physical activity time (2 games: 5 min of movement and active breaks), a balanced diet (2 games: healthy breakfasts and the cool recipe), and knowledge and reflection on healthy lifestyle habits (2 games: asking questions and my alien) (Figure 1(b)). The digital materials are embedded in a web platform that allows teachers to know the health status of the classroom based on the scores obtained by the students in each of the mini games. The games can be used in the classroom or at home, thus trying to facilitate parental interaction with the program (the digital materials were limited to a maximum of 30 min per day, with an emphasis on active learning and classroom‐based use, minimizing risk of screen overexposure. Additionally, all content was gamified to promote physical activity, not passive screen use. No minimum time limit was imposed for the study). It is important to emphasize that we will always work with the classroom score, emphasizing that health is everyone’s responsibility.

The family component of the intervention was primarily designed to reinforce school‐based learning through home engagement. Children were encouraged to use both paper‐based materials and digital tools outside the classroom, facilitating indirect parental involvement. While no formal parent training sessions were implemented, families had access to all materials and were encouraged to participate in activities, particularly those related to nutrition and lifestyle habits. This approach was intended to extend behavior change beyond the school environment while maintaining feasibility within a large‐scale intervention.

FIGURE 1Developed materials. (a) Printed material and (b) digital material.

**Figure figpt-0001:**
[figure not shown]
(a)

**Figure figpt-0002:**
[figure not shown]
(b)

#### 2.3.1. Intervention Delivery and Implementation

The program was initiated with an evaluation phase (April–June 2022) and a teacher training phase (April–June 2022) before initiating the implementation over one academic year (September 2022 to June 2023) and integrated into routine classroom activities. Teachers were responsible for implementing the intervention components within their usual teaching schedule.

The paper‐based materials (workbooks) were aligned with the official primary education curriculum (Decree 89/2014) and designed to be incorporated into subjects such as natural sciences, physical education, and tutoring sessions. Teachers were encouraged to deliver activities on a regular basis throughout the school year, typically integrating them into weekly classroom sessions. While a standardized set of materials and objectives was provided, teachers retained flexibility to adapt the timing and pacing of activities according to classroom needs.

Digital materials consisted of six gamified applications targeting physical activity, nutrition, and healthy lifestyle knowledge. Teachers were encouraged to incorporate these tools periodically during classroom time and to promote their use at home. Although no strict minimum usage was imposed, digital exposure was limited to a maximum of 30 min per day, with an emphasis on active engagement rather than passive screen time.

The intervention followed a semistructured approach: core content and materials were standardized across schools, while allowing adaptability in delivery to enhance feasibility and real‐world applicability. Post‐intervention measurements were taken in April–June 2023 (will be reported separately). Table 1 summarizes the schedule of enrollment, interventions and assessments.

**TABLE 1 tbl-0001:** SPIRIT schedule of enrollment, interventions, and assessments.

Study period	Activity	Enrollment (T0)	Baseline	Intervention	Post‐intervention
Enrollment	Informed consent	X			
Enrollment	Eligibility screening	X			
Assessments	Anthropometric measurements		X		X
Assessments	Physical activity (accelerometry)		X		X
Assessments	Body composition		X		X
Assessments	Metabolic parameters (glucose and lipids.)		X		X
Intervention	Multicomponent school‐based education			X	
Intervention	Teacher training	X	X	X	
Outcomes	Primary and secondary outcomes (e.g., BMI z‐score)				X

##### 2.3.1.1. Control Arm

The control group was measured at the same time as the intervention arm. No implementation was planned for the control schools.

#### 2.3.2. Implementation Fidelity and Adherence

In order to ensure fidelity of implementation of the intervention, Likert‐type scales for teacher self‐assessment and external observation were designed. These scales have 5 response options (0 = never to 4 = always), with a mean score ≥ 3 considered indicative of adequate fidelity. Teachers also recorded the number of intervention sessions delivered throughout the academic year, allowing quantification of exposure to the intervention. Adherence to the intervention was monitored through these logs and evaluation tools, enabling assessment of both the consistency and intensity of implementation across participating schools.

### 2.4. Outcome Measures

Our primary outcome is the change in body mass index (BMI). WHO growth curves were used to define overweight and obesity [21]. BMI was selected as the primary outcome due to its wide acceptance, ease of measurement, and comparability with national and international surveillance systems (e.g., WHO, ALADINO, and COSI). While BMI has limitations—notably its inability to distinguish fat mass from lean mass—it remains the most standardized and feasible anthropometric measure for large‐scale interventions in pediatric populations. Previous trials and systematic reviews comment on the use of BMI *z*‐score as an outcome in school‐based obesity prevention programs [22–24]. In our study, BMI was complemented by additional measures such as body fat percentage, waist circumference, and metabolic markers, allowing for a more nuanced understanding of body composition and health outcomes.

Secondary outcomes are changes in triponderal mass index (TMI), weight, body fat percentage, waist circumference, physical activity, and metabolic parameters.

Anthropometric measurements included weight, height, BMI, TMI, body fat percentage, and waist and hip circumferences. Healthcare personnel conducted the measurements at the schools attended by the children. Standardized conditions were adapted from the 2019 ALADINO study in the Canary Islands [25]. The WHO definition of overweight and obesity was used to define overweight and obesity: overweight and obesity are defined as “BMI‐for‐age and weight‐for‐height with more than one and two standard deviations (SDs), respectively, above the median of the WHO child growth standards” for > 5 years. The measurements were taken using a Tanita model DC‐360 impedance scale (Tokyo, Japan) for weight and body fat percentage, a portable TANITA stadiometer (Leicester model) for height, and a flexible, nonstretchable anthropometric measuring tape for waist and hip circumference. Nutritional ultrasound was performed using an L6C transducer (Microcaya) on a subset of children who provided consent for blood sample analysis. The ultrasound measurements focused on quantifying subcutaneous abdominal fat and preperitoneal fat tissue thickness. While the results are not presented in this manuscript, these measurements were collected to assess body composition and fat distribution in the context of obesity prevention.

Physical activity was objectively assessed in a random sample of 74 participants using the GENEActiv accelerometer (Activinsights Ltd., Kimbolton, United Kingdom). The participants were instructed to wear the accelerometer on their dominant wrist for 8 consecutive days and nights, including both weekdays and weekend days. Data were processed using RStudio software version 2022.07.2 + 576 (RStudio Team [2022]). RStudio: Integrated Development Environment for R. Boston, MA: RStudio, PBC) and the accelerometer manufacturer provided the processing algorithm for data segmentation and classification. The GENEActiv accelerometer is a triaxial accelerometer that measures acceleration in three orthogonal planes (*x*, *y*, *z*), which was configured at a sampling rate of 100 Hz. From the raw acceleration data, the processing algorithm provides activity intensity metrics, including time spent in sedentary, light, moderate, and vigorous physical activity. Classification is based on the vector magnitude of the acceleration signals. Specifically, the software calculates the Euclidean norm minus one (ENMO) of the acceleration signals, which provides a measure of the dynamic acceleration. For this study, only data relating to moderate and vigorous physical activity were considered. The number of participants was chosen based on the number of available accelerometers and available time for its use. We chose participants aged 8–9 years, in order to facilitate comparison with the PASOS 2019 study [26], the largest national study performed to date in Spain looking at the physical activity of children. We randomized the number of participants based on the type of school and arm (intervention vs control), aiming for a 1:1 ratio: 38 participants came from public schools and 36 from private and partially subsidized centers. A total of 37 participated in the intervention arm and 37 in the control arm.

Accelerometry data were analyzed separately for school days and nonschool days. For school days, we further stratified the analysis into two time periods: school hours (08:30 to 16:00) and after‐school hours (16:01 to 21:00), to distinguish between physical activity performed during school time and outside school hours. Minimum use included full use of the accelerometer during the study period (24 h/d for 8 days).

Metabolic parameters: fasting peripheral blood samples were taken from consenting participants (whose families had also given written consent) in two tubes with ethylenediaminetetraacetic acid (EDTA) and no additives, respectively. Samples were centrifuged and plasma and serum were separated.

The following tests were obtained using standardized, automatic methods: blood count was assessed in total blood, and C‐reactive protein (CRP), glucose, creatinine, transaminases, total and HDL cholesterol, triglycerides, and insulin were measured in serum. Insulin was measured with a chemiluminescent immunoassay using paramagnetic particle technology on the DXI 800 analyzer (Beckman Coulter, Brea, CA). HOMA index was calculated with the following formula: HOMA‐IR = (fasting glucose (mg/dL)  × fasting insulin (μUI/mL))/405. Glucose metabolism disorders were classified according to ADA criteria [27]. Impaired fasting glucose was defined as a fasting glucose value of 100–125 mg/dL. Dyslipidemia was diagnosed based on international recommendations [28]. Hypercholesterolemia was defined as total cholesterol > 200 mg/dL.

Other variables: although the intervention addressed behaviors such as eating habits, screen time, and sleep hygiene, these were not quantitatively assessed at baseline due to time and resource limitations. Their inclusion in subsequent evaluations is planned.

It is worth mentioning that post‐intervention results will not be presented here.

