At the end of the study, the primary and secondary outcomes will be reassessed. The primary analysis will be conducted according to the intention‐to‐treat (ITT) principle, where all randomized participants will be analyzed according to their assigned treatment group, regardless of adherence or withdrawal. Missing data will be handled using multiple imputation techniques. The treatment effect for each outcome will be estimated using appropriate statistical models, adjusting for baseline values of the outcome and other relevant covariates. Multivariate linear and logistic regression models will be used to evaluate intervention effects, adjusting for baseline covariates such as age, sex, and school type. Interaction terms will explore effect modification by SES and baseline BMI category. All multivariate analyses will adjust for school type as a proxy for SES, given its known association with childhood obesity and its imbalance between study arms. No changes to the methodology were implemented after trial commencement.

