### 3.3. Physical Activity

Daily moderate/vigorous activity was, on average, 4.2 ± 1.2 h (252 ± 72 min), with significant differences between school and nonschool days (*p* < 0.001) (Figure 2(a)), and between morning (8:30–16 h) and afternoon (16:00 to 21:00 h) intervals (*p* < 0.001) (Figure 2(b)). We found statistically significant differences in moderate/vigorous activity during the school day mornings and afternoons among center types (*p* < 0.05) (Figures 3(a) and 3(b)). No significant differences were found between control and intervention groups (*p* = 0.74) or between boys and girls (*p* = 0.73). We did find a significant, inverse correlation between the amount of moderate/vigorous physical activity during school days and the BMI of the subjects (*r* = −0.26; *p* = 0.02).

FIGURE 2Average moderate/vigorous activity time in minutes per day. (a) During school and nonschool days and (b) during school day mornings and afternoons.

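### The accelerometer minimum is full wear with no tolerance; applied literally at both waves, it would cost precision and select on compliance in a 74-child secondary outcome

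*Protocol article*

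**What the plan says.** Section 2.4 tells children to "wear the accelerometer on their dominant wrist for 8 consecutive days and nights, including both weekdays and weekend days". It then sets the criterion: "Minimum use included full use of the accelerometer during the study period", specified as 24 hours a day for 8 days. It gives no allowance for non-wear, no definition of a valid day and no minimum number of days.

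The same section says "Physical activity was objectively assessed in a random sample of 74 participants" and "A total of 37 participated in the intervention arm and 37 in the control arm". The number was set by how many devices were available and for how long. School days are analysed in two windows, 08:30 to 16:00 and 16:01 to 21:00, and non-school days are analysed separately.

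Change in physical activity is listed as a secondary outcome (Section 2.4), and Table 1 schedules accelerometry at baseline and after the intervention. Section 2.5 plans an intention-to-treat analysis and states "Missing data will be handled using multiple imputation techniques". At baseline, Section 3.3 reports an inverse correlation between the "amount of moderate/vigorous physical activity during school days and the BMI of the subjects", with r = −0.26 and p = 0.02, and gives no separate count of children analysed.

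**The concern.** A minimum equal to 100% of the instructed time is an all-or-nothing rule. It covers 8 × 24 = 192 consecutive hours, while the school-day windows span 12.5 hours of each day. A gap during sleep removes nothing from those windows, but taken literally it puts the record below the minimum.

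Two things would be at stake if the rule were enforced as written:

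- **Precision.** The sample is small and has no stated allowance for non-wear. Change requires an acceptable record at both waves.
- **Selection.** The children kept would be those who never took the device off, who need not represent the children sampled.

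The article states a criterion here, so this is not a detail left to a fuller document. What it leaves open is what happens to a record that falls short.

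**Working it through.** **1. The plan's own count.** By arm, 37 + 37 = 74. By school type ("38 participants came from public schools and 36 from private and partially subsidized centers"), 38 + 36 = 74. The sample size is consistent.

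**2. How many children were in the baseline correlation?** Inputs are r = −0.26 and p = 0.02 (Section 3.3). The formula is t = r√((n − 2)/(1 − r²)), two-sided on n − 2 degrees of freedom.

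- n = 74, |r| = 0.26: t = 2.285, p = 0.025. Over the rounding range of |r| (0.255 to 0.265), p runs from 0.028 to 0.0225, which is compatible with the printed 0.02.
- n = 72, |r| = 0.265: p = 0.0245, which rounds to 0.02.
- n = 71, |r| = 0.265: p = 0.0255, which rounds to 0.03.

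If both figures were rounded, n was at least 72. If p was truncated rather than rounded, the lower limit is 68 (p = 0.029 at |r| = 0.265; p = 0.0302 at n = 67). The baseline correlation therefore lost at most 2 of the 74, or at most 6.

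**3. What literal enforcement could cost (illustration only).** The documents give no wear rate. Assume that each child-day is fully worn with probability q, independently across days and waves. The share qualifying is q⁸ at one wave and q¹⁶ at both.

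| q (assumed) | q⁸ | qualifying at one wave | q¹⁶ | qualifying at both |
|---|---|---|---|---|
| 0.99 | 0.923 | 68 of 74 | 0.851 | 63 of 74 |
| 0.98 | 0.851 | 63 of 74 | 0.724 | 54 of 74 |
| 0.95 | 0.663 | 49 of 74 | 0.440 | 33 of 74 |

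**4. Detectable difference.** Settings: two-sample t-test, 5% two-sided, 80% power, SD 72 min/day (baseline, Section 3.3), no clustering.

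- 37 per arm: d = 0.66; 0.66 × 72 ≈ 47 min/day
- 27 per arm (54 children): d = 0.777; 0.777 × 72 ≈ 56 min/day
- 16 to 17 per arm (33 children, taken as 16.5): d = 1.007; 1.007 × 72 ≈ 72 min/day

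**The case against.** A reader might draw four stronger conclusions. The documents support none of them.

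- **That any removal excludes a child.** Nothing states the consequence of falling short or how non-wear is detected. Exclusion is the natural reading of a minimum, but it is an inference.
- **That the rule has already shrunk the sample.** Step 2 points the other way: almost all 74 were analysed at baseline.
- **That the rule was therefore not applied.** The same count fits near-complete wear, or 74 being only the children who met the criterion, equally well.
- **That the rule contradicts the missing-data plan.** A wear rule can decide which records are valid, and imputation can then handle the rest. Imputation would not remove bias if non-wear depended on unobserved activity, but that is a limitation, not a contradiction. The documents do not say why devices were removed, if they were.

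The illustration is also open to attack, and fairly. Wear habits probably cluster within children, so joint loss would be smaller than under independence. The SD of 72 min/day is a baseline spread, not the SD of change or of a baseline-adjusted residual. If 74 children were fitted, the rule was enforced and 72 met it, the same rate at follow-up would leave 72²/74 ≈ 70 children. The detectable difference would then move only to about 49 min/day (35 per arm, d = 0.679). On that reading the 98% row, which expects 63 at baseline, is too pessimistic.

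What stands is that the stated criterion has no tolerance, is broader than the school-day windows it serves, and comes with no account of how many children met it.

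**Conclusion.** The criterion is badly fixed, and the point is minor. Taken literally at both waves, it would put usable records below the minimum and make validity depend on compliance, for one secondary outcome in 74 children. The primary BMI outcome is not affected.

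No actual loss is shown. At least 72 children (about 68 if p was truncated) were analysed at baseline, and the article leaves three explanations open: near-complete wear, a count of compliers only, or a rule not enforced. Only the first is harmless. In the second case the 74 are no longer simply a random sample. In the third the published rule is not the one used, and follow-up could be processed differently.

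The size at follow-up is conditional. The rise from about 47 to about 56 or 72 min/day rests on assumed daily full-wear of 98% or 95%, independence across days and waves, complete-case use of both waves, the baseline SD and no clustering. If follow-up compliance matches 72 of 74, the rise is about 1 to 2 min/day.

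**What to change.** Before the follow-up accelerometry is analysed:

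1. State the rule actually used at baseline, and whether 74 is the number fitted or the number meeting it.
2. Replace full wear with a valid-day rule tied to the analysed windows: a minimum of wear hours within 08:30 to 21:00, and minimum numbers of school and non-school days.
3. Apply the same rule to both waves.
4. Include children with partial valid wear in the school-clustered model already planned.
5. Report the numbers meeting each criterion by arm and wave, and keep full wear as a sensitivity analysis.

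The cost is rewording and reprocessing of recordings; no new fieldwork is needed. The downside is that some included children contribute fewer observed days, so their averages are less precise.
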